### Data analysis

In the primary outcome analysis of the audit intervention, CR centres in clusters B and C will be compared. All CR centres that have responded to the CR structure and process variables will be included in the analysis. For the primary outcome analysis of the implementation support intervention CR centres in clusters A and B will be compared. All CR centres that have i) provided answers to the structure and process variables and that ii) have scores in the lower two tertiles of the adherence score at baseline will be compared. Our analyses will assume intention-to-treat principles by treating intervention assignment as randomized regardless of whether the intervention had uptake within the practice. If not all centres in cluster A accept implementation assistance, a per-protocol analysis will be performed including only those centres in study group A that accept implementation assistance.

For the secondary analyses on patient outcomes, all patients that attended at least two follow-up visits within CR will be included. For the outcome analysis of the audit intervention patients followed at CR centres in clusters B and C will be compared. For the outcome analysis of the implementation support intervention patients followed at CR centres in clusters A and B will be compared. A per-protocol analysis will be performed including only patients belonging to CR centres in cluster A that accept implementation assistance.

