### Randomization

Centres will be randomized 1:1:1 to three clusters (A, B and C). Randomization will be stratified by geographical healthcare district (two districts in each stratum). Randomization will be performed by an independent organisation not involved in the study to avoid site-selection bias.

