### Sample size calculations

As the number of CR centres is fixed, sample size calculations have been performed to estimate the difference in mean adherence score the study will be able to reveal. For this purpose, in a feasibility analysis the CR structure and process variables were collected from 8 CR centres of different sizes and geographical locations. The mean adherence score was 30.8 (standard deviation [± 2.4]) out of a maximum available score of 39. For the audit intervention, given the following presumptions:

23 out of possible 26 CR centres in each group (minimal drop-out is anticipated).Power of 80%.An alpha value of 0.05.

The study will have the power to identify a difference of ± 2.0 in adherence score between centres in cluster B (randomized to having variables on CR structure and processes incorporated in the SWEDEHEART registry) and cluster C (no new variables incorporated).

For the implementation support intervention, only centres in the lower 2 tertiles of the adherence score at baseline (approximately 17 centres) will be offered implementation support. Given the following presumptions:

14 out of possible 17 centres in each group (minimal drop-out is anticipated).Power of 80%.An alpha value of 0.05.

The study will have the power to identify a difference of ± 2.5 in adherence score between centres in cluster A (randomized to receiving implementation support) and cluster B (no implementation support).

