### Quantitative data

For baseline characteristics descriptive statistics will be used (means +/-standard deviation, medians [quartile 1, quartile 3], proportions [%] and ranges). For the primary outcome analysis, given randomized treatment assignment, total adherence scores at end of follow-up as well as change in scores between baseline and follow-up will be compared using linear regression analysis. In the case of unequal randomization concerning CR centre size (small < 75 patients/year, medium 75–150 patients/year or large > 150 patients per year), geography (6 geographical districts in Sweden, two in each stratum) or the centres belonging to a university hospital (yes/no), adjusted multivariable analysis will be performed. Results will be reported as relative treatment effects (odds ratios) with 95% confidence intervals. For secondary outcome analysis on short-term patient outcomes, the same statistical methods will be used, applying linear (continuous) or logistic (binary) regression analyses. For long-term outcomes (major adverse cardiovascular events [MACE] and total mortality) Cox proportional hazards regression models will be performed, reporting hazard ratios with 95% confidence intervals. In case of missing data, imputation will be considered. For all quantitative analyses a two-sided test of statistical significance will be used with an alpha level of 0.05.

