### Strengths and limitations

A strength of our study is that patient-level data will be retrieved from coherent and consistent quality registries with national representability. On centre-level, the research team has a vast collegial network in Sweden, which is anticipated to aid in cultivating trust and engagement in the study. As for all implementation interventions, possible recruitment and retention barriers might be encountered, with possible lack of local leadership support and resistance to change in practice. At the same time, the facilitators will closely collaborate with CR teams to evaluate potential opportunities and obstacles. They will provide support and aim to establish trusting relationships with members of the teams. In the event of disruptions, their role will involve assisting the teams in effectively navigating and resolving these challenges.

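### The per-protocol analysis filters cluster A, but not cluster B, on acceptance of support after randomisation, so randomisation no longer protects the contrast and it may be biased

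*Protocol article*

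**What the plan says.** The main A versus B analysis in the protocol article (Data analysis) follows intention-to-treat. It is limited to responding centres in the lower two tertiles of the baseline adherence score.

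A per-protocol analysis is added at two levels. At centre level, if not every cluster A centre accepts, "a per-protocol analysis will be performed including only those centres in study group A that accept implementation assistance". At patient level, "A per-protocol analysis will be performed including only patients belonging to CR centres in cluster A that accept implementation assistance". Neither sentence names the comparator. The patient-level text also states no tertile limit, for the main or the per-protocol comparison.

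Four other places bear on what acceptance means:

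- The implementation support intervention: directors or key stakeholders are approached by e-mail and, on accepting, are asked to free staff time.
- Ethical considerations and withdrawal criteria: participation needs verbal consent and then a letter of intent signed by the director.
- The timeline (Table 3): randomisation is in Q3 2023, and support starts in Q2 2024.
- Strengths and limitations: the authors foresee possible recruitment and retention barriers, with "possible lack of local leadership support and resistance to change in practice".

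**The concern.** Acceptance is decided after allocation and is observed in one arm only. Removing decliners from A leaves a selected subset, while the B centres that would have declined stay in the comparison. Whatever separates accepting from declining centres then becomes part of the estimated effect of support.

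The outcome is a change of practice towards guidelines. Leadership and readiness to change, which the authors mention as possible obstacles to participation, could well influence that outcome without any support. The adjustment under Quantitative data would not repair this. It is triggered by imbalance in centre size, geography or university status, and none of these measures leadership or readiness.

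At stake is the reading of any per-protocol result. It is planned for both the adherence score and patient outcomes, and the article does not mark it as supportive. The cost-effectiveness section builds on the effect of support on patient outcomes without saying which estimate it will use.

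**Working it through.** **Inputs from the protocol article.** The SD comes from the feasibility sample of 8 centres: "The mean adherence score was 30.8 (standard deviation [± 2.4]) out of a maximum available score of 39". The A versus B comparison assumes 14 of a possible 17 centres per group, 80% power and a 5% level. Quantitative data specifies "a two-sided test of statistical significance will be used with an alpha level of 0.05".

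**The plan's own figure.** Detectable difference = SD × √(2/n) × (z₀.₉₇₅ + z₀.₈₀) = 2.4 × √(2/14) × (1.960 + 0.842) = 2.54. The stated 2.5 reproduces, and power at 2.5 is 78.7% by the normal approximation. The SD of 2.4 and the 2.5-point yardstick are therefore the plan's own basis for this comparison.

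**Assumed inputs.** The article gives neither the acceptance rate nor the link between willingness and outcome.

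- Acceptance: 10 to 14 of 17. The upper end is the number that the sample size section expects to keep. The lower end is an assumption. Qualitative data expects about 10 to 12 interviews depending on how many centres accept, which is compatible with it but can be read in more than one way.
- Correlation ρ between willingness to accept and the follow-up score: 0.2 to 0.5.

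**Bias with no true effect.** Suppose the k most willing of 17 eligible A centres accept and are compared with 17 eligible B centres, unfiltered. The expected spurious difference is ρ × SD × m, where m is the mean of the k largest of 17 standard normal values.

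| Accepting | m | ρ = 0.2 | ρ = 0.5 |
|---|---|---|---|
| 14 of 17 | 0.295 | 0.14 | 0.35 |
| 12 of 17 | 0.464 | 0.22 | 0.56 |
| 10 of 17 | 0.631 | 0.30 | 0.76 |

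For example, 0.5 × 2.4 × 0.631 = 0.76. If acceptance follows a fixed threshold instead of a fixed count, m becomes φ(z)/p with p the accepting share. The corners are then 0.2 × 2.4 × 0.315 = 0.15 and 0.5 × 2.4 × 0.661 = 0.79. Rounded, the range is 0.15 to 0.8, or 0.15/2.5 = 6% to 0.8/2.5 = 32% of the 2.5-point target.

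**Cross-check without a correlation.** Bias = (acceptor mean − decliner mean) × share declining. A 2-point gap with 10 of 17 accepting gives 2 × 7/17 = 0.82. With 14 of 17 it gives 2 × 3/17 = 0.35.

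**Effect on the test.** In a simulation of 40,000 null trials (t-test, 17 B centres), the nominal 5% test rejected as follows:

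- 14 of 17 accepting: 5.9% at ρ = 0.3 and 7.0% at ρ = 0.5.
- 10 of 17 accepting: 7.6% at ρ = 0.3 and 12.2% at ρ = 0.5.
- ρ = 0: bias zero to within simulation error, rejection about 5%.

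**If upper-tertile B centres were included.** Under normality the lower two tertiles lie 0.545 SD below the full mean at baseline, and 0.545 × 2.4 = 1.3 points. A comparator that took in all of B would shift the contrast against support.

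**The case against.** The strongest reply is that intention-to-treat is the declared main analysis, and per-protocol is additional and, at centre level, conditional on some refusal. That stands: the primary conclusion does not depend on this point.

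A reader might infer that accepting A centres are to be compared with all of cluster B. The article does not say so. The comparator is unnamed, and the primary A versus B set is limited to the lower two tertiles, so eligible B centres are the natural centre-level reading. Only the patient-level wording is open to all of B, and that reading would push the result against support.

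A reader might also infer that a false benefit is certain. It is not. The remarks on leadership and resistance are hedged and are not given as the reasons for refusal. Centres might accept because they are weaker, which would lower their end scores. With zero correlation there is no bias, and if every centre accepts there is no selection.

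The size calculated here applies to an unadjusted follow-up score. The plan also compares change scores, which would largely remove any selection already reflected in the baseline score, though not a different propensity to improve.

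Finally, details of a secondary analysis are often left to the statistical analysis plan. That excuses the unnamed comparator. It does not excuse the rule that the article does state, which filters one arm on a post-randomisation decision.

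**Conclusion.** The point holds in a limited form. As stated, the per-protocol rule gives a non-randomised contrast at centre and patient level, because acceptance can be observed only in cluster A. Bias in favour of support is plausible but not established.

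For the unadjusted follow-up score with no true effect, it amounts to about 0.15 to 0.8 points against the 2.5-point target. This assumes SD 2.4, 10 to 14 of 17 centres accepting and a correlation of 0.2 to 0.5. The last two are assumptions, and a zero correlation gives zero bias. The intention-to-treat result and the sample size figures are unaffected. The rule should be changed, but it does not threaten the main conclusion.

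**What to change.** **Adherence score.** Replace the naive contrast with a complier-average effect among lower-two-tertile centres in both A and B. Use two-stage least squares with randomised arm as instrument and acceptance as treatment received, adjusted for baseline score and stratum. Cluster B has no access to support, so non-compliance is one-sided and the estimate is in essence the intention-to-treat difference divided by the acceptance rate. If the naive contrast is kept, name its comparator and label it supportive and non-randomised.

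**Patient outcomes.** Apply the lower-two-tertile limit to both clusters. Use the same instrument, clustered on centre, for continuous outcomes and for binary outcomes on the risk-difference scale. Two-stage least squares does not carry over directly to the planned odds ratios or Cox hazard ratios. For time-to-event outcomes, rely on intention-to-treat and label any per-protocol result supportive.

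**Cost.** No new data and a little more analysis work. The interval widens. Before covariate adjustment and with 17 eligible centres per arm, the intention-to-treat standard error is 2.4 × √(2/17) = 0.82. Dividing by the acceptance rate gives about 0.82 × 17/14 = 1.00 with 14 accepting, or 0.82 × 17/10 = 1.40 with 10. The naive contrast has 2.4 × √(1/14 + 1/17) = 0.87 and 2.4 × √(1/10 + 1/17) = 0.96. The method also assumes that merely being offered support has no effect in centres that decline it, which should be stated.

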## Method

### Study setting and recruitment

The study started in October 2023 and will include all CR centres (*n* = 78) which report to the SWEDEHEART-CR registry. The sole exclusion criterion for CR centres is unwillingness to participate. The inclusion criteria for patients are 1) having a diagnosis of a type 1 MI (caused by atherosclerotic plaque rupture or coronary artery thrombosis) and 2) age 18–79 years at discharge from MI hospitalization. There are no exclusion criteria for patients.

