### Primary effectiveness outcome

The primary endpoint is an “adherence score”, measuring adherence to the National Guidelines on Secondary Prevention [15]. The adherence score is partly derived from the 30 variables capturing guideline-directed CR structure and processes incorporated into the SWEDEHEART-CR registry in October 2023. Permissible values are yes/partly/no/unknown. Additionally, the adherence score will include nine process variables that measure a) patient attendance in various CR components (number of patients attending a CR programme component divided by the number of patients eligible for participation), and b) time between MI hospitalization discharge and start of different CR programme components, already audited in SWEDEHEART:

*Attendance in CR components*
Proportion of patients attending an initial CR assessment (nurse visit).Proportion of patients attending an individual visit to a physiotherapist after discharge before starting an exercise-based CR (EBCR) programme (a pre-exercise screening visit).Proportion of patients completing a 3-month EBCR programme.Proportion of patients attending an individual close-out visit to a physiotherapist after completing an EBCR programme (a post-exercise assessment visit).Proportion of patients attending a patient education programme.Proportion of patients attending a close-out CR visit with a nurse at one-year after MI.*Time (days) to start of different components of CR*7.Time from hospital discharge to initial CR assessment (nurse visit).8.Time from hospital discharge to the pre-exercise screening visit to a physiotherapist.9.Time from pre-exercise screening visit to start of EBCR programme.

The responses will be pooled at each site into an adherence score for each CR centre. The contribution of each variable to the score will be weighed depending on the importance of each measurement, based on level of recommendation in European guidelines [1].

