### Secondary effectiveness outcomes

Table 2 displays secondary outcomes, encompassing both short- and long-term patient outcomes and implementation outcomes. Implementation outcomes will be based on responses gathered through the customized Normalisation Measure Development (NoMAD) questionnaire [29] and insights obtained from focus group interviews, as well as a cost-effectiveness analysis.

**Table 2 Tab2:** Secondary outcomes

Outcomes	Cluster	Measures	Data source	Timing
Short-term patient-level outcomes	All clusters	- Blood pressure (mmHg). - LDL-C (mmol/L). - Self-reported statue of health measured using EuroQol-VAS (0–10). - Self-reported smoking status (never/ prior [> 1 month smoke-free]/active) - Self-reported dietary habits (four questions with Likert scale 0–3 points, total score 0–12 points). - Self-reported physical activity (the number of days during the last week the patient has been physically active for a minimum of 30 min [at least 10 min at a time] with activity causing shortness of breath and a slightly increased pulse, corresponding to a brisk walk). - Completing an exercise-based CR programme for at least 3 months (yes/no)	The SWEDEHEART registry	Baseline and one-year after the start of intervention
		- Adherence to secondary prevention medication	Pharmaceutical registry	Baseline and one-year after the start of intervention
Long-term patient-level outcomes	All clusters	Total mortality Major adverse cardiovascular events (MACE) consisting of the following: - cardiovascular mortality - non-fatal MI - non-fatal ischemic stroke - coronary revascularization - hospitalization for new or worsening heart failure	National Patient Registry and the Cause of Death Registry	Up to 5 years after the end of the intervention
Centre-level implementation outcomes	Cluster A	- Barriers - Facilitators	Semi-structured focus group interviews	At the start and the end of implementation support period
		- Implementation cost and cost effectiveness.	A comparative health economic evaluation	At the start and the end of implementation support period

*LDL-C* low-density lipoprotein cholesterol, *VAS* visual analogue scale, *CR* cardiac rehabilitation, *MI* myocardial infarction

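### Patient-outcome analyses keep only patients with at least two CR visits, a post-randomisation condition that is avoidable for mortality, MACE and medication and drops deaths before the second visit

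*Protocol article*

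**What the plan says.** The rule is in the Data analysis section of the protocol article. For the secondary analyses of patient outcomes, "all patients that attended at least two follow-up visits within CR will be included". Patients in clusters B and C are then compared for the audit intervention, and patients in A and B for implementation support.

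Table 2 (Secondary effectiveness outcomes) places under patient-level outcomes the short-term risk factors, completion of an exercise-based programme, medication adherence, total mortality and MACE. No separate population is given for the long-term outcomes. Mortality and MACE are taken from the "National Patient Registry and the Cause of Death Registry", and medication from the pharmaceutical registry. The remaining short-term measures come from SWEDEHEART.

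The unit of allocation is the centre: "Centres will be randomized 1:1:1 to three clusters (A, B and C"). Table 3 puts randomisation in Q3 2023.

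The Primary effectiveness outcome section builds attendance into the adherence score. Its items include "Proportion of patients attending an initial CR assessment (nurse visit") and "Proportion of patients attending a close-out CR visit with a nurse at one-year after MI". The denominator for attendance items is eligible patients: "number of patients attending a CR programme component divided by the number of patients eligible for participation".

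**The concern.** Whether a patient reaches two visits is known only after the centre has been randomised, and it may depend on the arm. It is also related to what the trial tries to change, since six of the 39 variables in the adherence score are attendance or completion proportions. If an intervention changes who attends, it changes who enters its own patient-level analysis, and centre randomisation no longer guarantees comparable patients.

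For registry outcomes nothing is gained by the restriction, because deaths, MACE and dispensed medication are recorded without a CR visit. A patient who dies before a second visit can never qualify, so those deaths leave the mortality and MACE analyses. Any benefit gained by bringing would-be non-attenders into care is hard to see when the comparison arm's non-attenders are left out.

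Two secondary aims (the effect of audit and of implementation support on patient outcomes) depend on this set. So does the cost-effectiveness analysis, which uses the effect on patient outcomes.

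**Working it through.** The plan states no patient-level sample size, event count or attendance rate, so there is no figure of its own to reproduce. The centre-level sample-size figures do not bear on this point.

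**Step 1: which outcomes need the restriction?**

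| Outcome (Table 2) | Source | Needs a CR visit? |
|---|---|---|
| Total mortality, MACE | National registries | No |
| Medication adherence | Pharmaceutical registry | No |
| Exercise-programme completion | SWEDEHEART | No: a non-completer counts as no, and the adherence score already measures completion over eligible patients |
| Blood pressure, LDL-C, EuroQol-VAS, smoking, diet, activity | SWEDEHEART | In general yes; non-attenders have no value under any rule |

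The restriction is avoidable for the first three rows. As written, completion would also be reported on two denominators in one trial: eligible patients in the score, two-visit attenders in the patient analysis.

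**Step 2: what selection could do under a true null (assumed inputs).** Let p_c and p_t be the two-visit attendance proportions in the comparison and intervention arms. Let k be the event risk of the additional attenders relative to patients who attend under either arm. Assume that everyone who would attend in the comparison arm would also attend in the intervention arm. With no treatment effect,

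RR among included = [p_c + (p_t − p_c)·k] / p_t.

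Example: p_c = 0.80, p_t = 0.90, k = 2 gives (0.80 + 0.10 × 2)/0.90 = 1.00/0.90 = 1.11.

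| p_c, p_t | k = 1.5 | k = 2 | k = 3 |
|---|---|---|---|
| 0.80, 0.85 | 1.03 | 1.06 | 1.12 |
| 0.80, 0.90 | 1.06 | 1.11 | 1.22 |
| 0.70, 0.85 | 1.09 | 1.18 | 1.35 |

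Rearranged, RR − 1 = (p_t − p_c)(k − 1)/p_t. The bias is zero when p_t = p_c (with the same kinds of patients attending) or k = 1. It changes sign when either factor does, so its direction is not fixed.

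**Step 3: a smoother variant.** A standard normal latent risk acts on the log-odds of the event (slope 0.5 or 1) and of attendance (slope −0.5 or −1). Event risk is 10% or 20%, and attendance is 70% against 80%, 80% against 85%, 80% against 90%, or 75% against 90%. The apparent null hazard ratio, ln(1 − risk_t)/ln(1 − risk_c), runs from 1.01 to 1.14. The largest case (10% risk, slopes 1 and −1, 75% against 90%) has risks among the included of 0.0804 and 0.0908: ln(0.9092)/ln(0.9196) = 1.14.

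**Step 4: a continuous outcome.** If attendance propensity correlates ρ with a standardised outcome, its mean among attenders is ρ·φ(z)/p, where φ is the normal density and z is the quantile for attendance p. For p = 0.70 and 0.80, φ(z)/p is 0.497 and 0.350, a difference of 0.147. With ρ = 0.2 the null difference is 0.03 SD; with ρ = 0.4 it is 0.06 SD.

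**Step 5: early deaths.** Two attended visits are required, so death before the second one excludes the patient. Non-fatal events before it do not. The Quantitative data section names Cox models but gives no time origin, landmark or delayed entry. If the clock starts before the second visit, the interval up to that visit is also free of death by construction.

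**The case against.** **Only secondary outcomes are touched.** This stands. The primary endpoint is a centre-level score compared between centres, and the sample size and interim rule rest on that score.

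**A shift in attendance is possible, not established.** This stands in part. The audit adds 30 structure and process variables, while the attendance items were already recorded in SWEDEHEART. None of those items is two-visit attendance, and the score could rise with little change in it. But attendance counts towards the score that both interventions are meant to raise, and an analysis set should not depend on hoping that it stays level.

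**A reader might infer a contradiction with the eligibility text**, which says "There are no exclusion criteria for patients". The documents do not support that. The sentence sets trial eligibility, whereas the Data analysis rule defines an analysis set. Likewise, the intention-to-treat statement concerns centre assignment. An analysis set narrower than eligibility is a choice open to criticism, not a textual conflict.

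**A reader might infer that immortal-time bias is built in.** That depends on a time origin the article does not fix and may leave to an analysis plan. Starting the clock at the second visit would remove it, and immortal time shared equally by both arms is not in itself a between-arm bias. The loss of deaths before the second visit remains whatever the origin.

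**Visit-measured risk factors are missing for non-attenders under any rule.** This stands. Imputation or weighting replaces a selection with missing-data assumptions and does not restore randomisation. The article's statement that imputation will be considered does not help as it is, because the inclusion rule removes these patients before any imputation.

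**Conclusion.** The concern holds in a limited form. The two-visit rule conditions the patient-outcome analyses on post-randomisation behaviour related to the intervention target, so the arms may be differently selected. It is hard to justify for total mortality, MACE and medication adherence, which need no visit, and it drops every death before a second visit.

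A reader might go further and conclude that the rule biases results against the interventions by a known amount. The documents do not support this. The ranges above (risk ratio 1.03 to 1.35, hazard ratio 1.01 to 1.14, 0.03 to 0.06 SD) all rest on assumed attendance and risk patterns. They assume that the intervention adds higher-risk or, for the continuous outcome, worse-scoring attenders. Other patterns would push the other way, and equal attendance with equal case mix would leave no between-arm bias, though results would then describe attenders only. With roughly 10 000 MI patients a year, a larger sample would not remove any such bias.

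This should be fixed, but the primary result does not depend on it. It affects the secondary patient outcomes and the cost-effectiveness analysis that draws on them.

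**What to change.** 1. **Registry-sourced outcomes (mortality, MACE, medication).** Make the main set all eligible patients (type 1 MI, 18–79 years) attributed to a randomised centre by a rule that does not depend on attendance. One candidate is the centre whose eligible-patient denominator in the adherence score counts the patient. Start follow-up for mortality and MACE at hospital discharge, and state this as the Cox time origin.
2. **Exercise-programme completion.** Report it over all eligible patients, matching the score.
3. **Visit-measured risk factors.** Use the same denominator with multiple imputation or inverse-probability weighting for missing one-year values, and say plainly that the result rests on missing-data assumptions.
4. **Two-visit set.** Keep it as a sensitivity analysis, and report two-visit attendance by arm so that readers can judge the selection.

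The cost is modest. An attribution rule for non-attenders must be written, because the Data protection section links patients to the centre where they were followed and does not say how a patient never followed would be linked. The score's denominators suggest that eligible non-attenders can be counted per centre, but individual attribution in the research dataset needs confirming. More risk-factor values will be missing. Table 3 runs follow-up to 2030, which leaves time to make the change before the long-term analysis.
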